## Abstract

**Background:**

Self-management by people with type 2 diabetes is central to good health outcomes and the prevention of associated complications. Structured education to teach self-management is recommended by the National Institute for Heath and Clinical Excellence; however, only a small proportion of patients report being offered this education and even fewer attend. This study aims to evaluate the implementation of a new internet-based self-management intervention: *HeLP-Diabetes* (Healthy Living for People with type 2 Diabetes) within the National Health Service. Specific objectives are to *a)* determine the uptake and use of *HeLP-Diabetes* by services and patients; *b)* identify the factors which inhibit or facilitate use; *c)* identify the resources needed for effective implementation; *d)* explore possible effects of *HeLP-Diabetes* use on self-reported patient outcome measures.

**Methods/Design:**

This study will use an iterative design to implement *HeLP-Diabetes* into existing health services within the National Health Service. A two stage implementation process will be taken, whereby batches of General Practice surgeries and diabetes clinics will be offered *HeLP-Diabetes* and will subsequently be asked to participate in evaluating the implementation. We will collect data to describe the number of services and patients who sign up to *HeLP-Diabetes*, the types of services and patients who sign up and the implementation costs. Semi-structured interviews will be conducted with patients and health professionals and cohorts of patient participants will be asked to complete self-report measures at baseline, 3 months, and 12 months.

**Discussion:**

This study will evaluate the implementation of a new online self-management intervention and describe what happens when it is made available to existing National Health Services and patients with type 2 diabetes. We will collect data to describe the uptake and use of the intervention and the resources needed for widespread implementation. We will report on patient benefits from using *HeLP-Diabetes* and the resources needed to achieve these in routine practice. Interviews with key stake holders will identify, define and explain factors that promote or inhibit the normalization of new patterns of patient and professional activity arising from *HeLP-Diabetes*.

## Background

Diabetes is one of the most common long-term conditions in the UK affecting around 4.5 per cent of the population. It is a leading factor in the development of chronic illnesses and complications including coronary heart disease, renal failure and blindness, as well as reducing life expectancy [1]. Diabetes and related complications put considerable strain on health budgets with the estimated cost to the National Health Service (NHS) of £14 billion a year [2].

Self-management by the patient is central to good diabetes care [3-5], and structured education in which the knowledge and skills necessary for self-management are taught, has been found to provide a fourfold decrease in the risk of complications developing [6]. Structured education at diagnosis with annual reinforcement is recommended by the UK’s National Institute for Health and Clinical Excellence (NICE) for all people with type 2 diabetes (T2DM). However, only 8.7 per cent of people with T2DM who were newly diagnosed in 2008–2009 reported being offered structured education during 2009–2011 while only 3.6 per cent reported actually attending structured education [7].

Structured education, currently delivered as a group based activity, may be particularly unsuitable for people with caring responsibilities, some ethnic minority populations, those with physical disabilities and those who find group interactions challenging. With NHS resources unlikely to increase for such education and the poor referral and uptake of existing programmes there is an urgent need for new cost effective ways of delivering self-management education which are acceptable to patients and clinicians. The use of new information and communication technologies to improve health and health care is now a central part of NHS policy, and NHS Choices is already delivering a number of websites although many of these have yet to be evaluated.

The internet offers huge potential for delivering public health interventions [8]. Internet- based interventions have a number of potential benefits including convenience, accessibility, anonymity and may be cost-effective in delivering education to large numbers of people. Although the current evidence on the use of new technology in diabetes is still evolving, positive effects of such interventions have been demonstrated in several studies. A Cochrane systematic review of interactive healthcare applications looked at 24 randomised control trials (RCTs) in a range of chronic diseases including diabetes. It found mostly positive effects, with users tending to become more knowledgeable, feel better supported, with possible improved behavioural and clinical outcomes compared with non-users [9]. Another systematic review produced a narrative report of interactive computer-assisted technology in diabetes care [10]. It identified 14 studies that looked at HbA1c levels (a measure of glucose metabolism which reflects average blood glucose levels over six to eight weeks) and found that 6 of 14 studies demonstrated significant improvements in HbA1c. The interventions also appeared to improve healthcare utilisation with more foot examinations and HbA1c monitoring. Evidence from a recent systematic review of 16 RCTs suggests internet-based self-management programmes for people with T2DM can improve HbA1c [11]. This review suggested that these positive effects on HbA1c may decrease over time, which is similar to the effects of more traditional group-based self-management education on HbA1c which also show a similar decline in benefits over time [4,12,13].The American Diabetes Association standards for self-management education recognise the need for both initial training and subsequent on-going support to try and maintain the benefits of educational interventions [14]. Internet-based interventions are ideally suited to providing ongoing self-management support that could allow sustained improvements and long-term improvements in outcomes.

We have developed an internet based self-management intervention for people with T2DM: '*HeLP-Diabetes: Healthy Living for People with Type 2 Diabetes’*. The design of this complex intervention has been informed by theory and the needs and preferences of patients and health professionals. It has been developed using a process of participatory design with users (people with T2DM and health professionals) heavily involved in the conception and creation. *HeLP-Diabetes* takes a holistic view of self-management and addresses a wide range of patient needs including education, lifestyle changes, medicine management, emotional management, social support with forums and personal stories and also addresses how patients interact and work with health professionals. A facility to interface with patients electronic medical records has been designed to provide patients access to self-management metrics recorded by General Practice (GP) surgeries. The information provided on *HeLP-Diabetes* is based on NICE guidelines and has been developed to complement existing structured group education.

This study will explore the implementation of *HeLP-Diabetes* within the NHS, addressing the facilitators and barriers associated with initial and continued engagement by staff and patients and the resources required to make *HeLP-Diabetes* a viable part of routine diabetes care. This implementation study is being conducted in parallel to a randomised control trial of the *HeLP-Diabetes* intervention. The Medical Research Council (MRC) framework for complex interventions [15] stresses the importance of considering the implementation of complex interventions throughout the development and evaluation phases in a cyclical and iterative way. The data provided by this implementation study will provide additional outcome data to that provided by the trial including data that will be essential for commissioners of care such as data on what happens in practice, and what actions and resources are needed for successful implementation and realisation of potential benefits.

### Aim

To explore the implementation of *HeLP-Diabetes* within NHS GP surgeries and hospital and community based diabetes clinics.

### Objectives

a. To describe the uptake and use of *HeLP-Diabetes* by NHS services and patients.

b. To identify factors which inhibit or facilitate implementation.

c. To identify the resources needed for effective implementation.

d. To explore any effects of *HeLP-Diabetes* use on self-reported patient outcomes.

### Theoretical framework

Literature on the transfer of research into clinical practice consistently reports the process as unpredictable, slow and haphazard [16]. The explicit use of theory in implementation research may support a better understanding of the generalisability and replicability of implementation interventions [17]. The MRC framework emphasises that the development, evaluation and implementation of health care interventions requires a strong theoretical foundation [15].

We have selected Normalisation Process Theory (NPT) [18,19] to provide a theoretical underpinning to this study. NPT can be used as a theoretical framework to identify factors that promote and inhibit the routine incorporation of complex interventions into everyday practice. It explains how these interventions work in practice (or fail to), looking not only at early implementation, but beyond this to the point where an intervention becomes so embedded into routine practice that it 'disappears’ from view (i.e., it is normalised) [20]. We will use NPT as an explanatory framework to explore the implementation process and to guide interviews with NHS staff. The use of NPT will provide a transferable understanding of the success or failure of the *HeLP-Diabetes* integration into routine NHS practice, providing learning opportunities for future studies.

## Methods/Design

### Design

This will be a longitudinal cohort study using qualitative and quantitative methods.

### Setting

The study will be conducted in GP surgeries, community diabetes clinics and hospital based diabetes clinics within two inner city London boroughs: There are approximately 80 GP surgeries, two services providing a range of community diabetes clinics and three hospitals running diabetes clinics within these two boroughs. Our aim is to make *HeLP-Diabetes* available to up to 30 GP surgeries and all diabetes clinics. Within these boroughs there are 16,223 people on GP registers with a recorded diagnosis of diabetes [21]. Since T2DM accounts for 90% of all diabetes cases, there are up to 14,601 potential users of *HeLP-Diabetes* within these two boroughs.

### Procedure

The use of *HeLP-Diabetes* will be offered to GP surgeries and diabetes clinics free of charge for the duration of the study (30 months). *HeLP-Diabetes* will be made available to batches of GP surgeries and clinics (approx. 2 or 3 at a time). This will allow learning and experience gained from the implementation at each batch of sites to be transferred to subsequent ones. Once organisations have agreed to use *HeLP-Diabetes* they will be asked to opt-in to the research evaluation study. Organisations who opt-out of the research evaluation will still be free to use *HeLP-Diabetes* without participation in the research.

Staff working in services that agree to use *HeLP-Diabetes* will be asked to recommend its use to all suitable patients with T2DM and refer them to a training appointment with a researcher or a member of the clinical team. Suitable times to recommend the use of *HeLP-Diabetes* may include at annual diabetes reviews and when a patient is newly diagnosed. Staff will also be encouraged to maintain engagement with *HeLP-Diabetes* by encouraging patients to use it at appropriate times during routine consultations.

During training appointments patients will be registered on the *HeLP-Diabetes* site and shown how to use it. Each appointment will be tailored to the specific needs of the patient and will focus on an aspect of diabetes self-management important to the patient. At the end of the training appointment patients will be invited to take part in the research study evaluating the implementation of *HeLP-Diabetes*. Patients who agree to take part in the evaluation study will be asked to sign a consent form after reading the participant information sheet and having the opportunity to ask any questions. Patients who opt-out of the research evaluation will still be free to use *HeLP-Diabetes* without participation in the research.

### Ethical consideration

Ethical approval for this study was gained from the NRES Committee East Midlands-Leicester ref: 13/EM/0033.

### Recruitment

Recruitment will happen at both organisational and patient level.

Both organisations and patients will be recruited firstly to use *HeLP-Diabetes* and secondly to take part in the research evaluation of the implementation.

#### Organisational

Strategies being explored to recruit organisations to use *HeLP-Diabetes* include engagement of the Clinical Commissioning Groups (CCG), direct contacts with hospital and community based clinics and the assistance of the North Central London Research Consortium (NoCLOR) to recruit GP surgeries.

Staff in participating services who opt in to the research evaluation will be invited to take part in research activities on an opportunistic basis throughout the study period.

#### Patient

Once a GP surgery or diabetes clinic has agreed to use *HeLP-Diabetes,* recruitment to use *HeLP-Diabetes* at the patient level will begin. Health professionals in participating GP surgeries and clinics will be asked to recommend the use of *HeLP-Diabetes* to all patients with T2DM who meet the inclusion criteria and to refer them to a training appointment. At the end of training appointments, eligible patients will be asked to participate in the research study evaluating the implementation of *HeLP-Diabetes*.

### Sample

#### Staff

A range of staff from GP surgeries and diabetes clinics including consultants, salaried doctors, junior hospital doctors, general practice partners, general practice managers, practice nurses, community nurses, hospital diabetes nurses and reception staff will be recruited to participate in the research evaluation study. The aim is to represent a range of perspectives of the staff who contribute to the care of patients with T2DM on the implementation of *HeLP-Diabetes*.

#### Patient

To use *HeLP-Diabetes* and participate in the evaluation study, patients must be 18 or above, registered at participating GP surgeries, community diabetes clinics or hospital based diabetes clinics and have a diagnosis of T2DM. Patients will be excluded from the research evaluation if they are unable to provide informed consent, e.g. due to psychosis, dementia or severe learning disabilities, are terminally ill (life expectancy less than 12 months), unable to use a computer due to physical or mental impairment or possess English language skills insufficient to use the intervention.

### Implementation plan

An implementation plan has been devised by the research team which will be offered to all services. This plan includes the following steps; an initial meeting at the GPsurgery or clinic to explain the new *HeLP-Diabetes* service, a demonstration of *HeLP-Diabetes*, training for staff who will be using *HeLP-Diabetes* top-up training and support as necessary, training patients to use *HeLP-Diabetes*, follow up contact with patients, continued monitoring and feedback to staff, and the provision of training materials to staff and patients. Each GP surgery and diabetes clinic will be invited to work with researchers to tailor the implementation plan to the individual setting.

The researcher will spend time with staff to implement *HeLP-Diabetes* and to provide support and facilitate patient training appointments. Formal feedback from interviews with staff and patients and informal feedback such as lessons learned from training staff and patients will be used by the researcher to develop and refine the implementation procedures. The iterative design will allow the implementation plan to be tested out on a small scale, the researcher to learn from the experience and modifications to be made to plan before testing it on a another small number of services. This method will allow for difficulties and challenges to be explored and addressed, which may otherwise be missed by widespread implementation. Through the process of modifying the implementation plan based on feedback from patients and staff and by allowing the implementation plan to be tailored to individual sites, we hope to increase buy-in and ownership of *HeLP-Diabetes* by staff and reduce barriers to successful implementation.

### Outcomes

The study objectives will be addressed in the following ways.

a. To describe the uptake and use of *HeLP-Diabetes* by NHS services and patients.

The number of GP surgeries and diabetes clinics *HeLP-Diabetes* is offered to, and the numbers who take it up will be recorded. To describe the types of services that take up *HeLP-Diabetes* we will collect data including: the number of patients registered at the surgery or who attend the clinic (overall numbers and those with T2DM), socio demographics of the patient population and the number of staff. For GP surgeries we will also collect: Quality and Outcomes Framework (QOF) achievement and whether it is a training or non-training practice.

The number of patients who register on *HeLP-Diabetes* will be recorded and patient registration data will be used to describe the characteristics of patients who sign up. This data will include; year of birth, gender, ethnicity, the surgery or clinics they attend, duration of diabetes, existence of complications, how diabetes is currently managed; what help the patient would like with self-management, smoking status, internet access (home/public) and use of computer (basic/intermediate/advanced).

Data on *HeLP-Diabetes* use will be recorded automatically by the website software and Google Analytics and will include number of logins, length of time patients use *HeLP-Diabetes* per visit, pages that are visited and those that are not, and the tools, assessments, educational modules that are used and how often.

b. To identify factors which inhibit or facilitate implementation.

Semi-structured interviews will be conducted with key informants, both patients and health professionals and will be focussed on exploring the barriers and facilitators to implementation. The researcher will also keep detailed notes on the implementation process and document any challenges and successes.

c. To identify the resources needed for effective implementation.

A proforma will be used to collect quantitative data on the resources spent on implementing *HeLP-Diabetes*, which are predicted to be largely made up of staff and researcher time. Semi-structured interviews will be conducted with key informants, both patients and health professionals, to investigate the resources needed for effective implementation.

d. To explore the effects of *HeLP-Diabetes* on self-reported patient outcomes.

Patient participants will be asked to complete two self-report measures. The first will be the Problem Areas in Diabetes (PAID) scale [22] which is a health related quality of life and emotional distress measure. It is comprised of 20 items focusing on areas that cause difficulty for people living with diabetes including; social situations, food, friends and family, diabetes treatment, emotions, relationships with healthcare professionals and social support. The second measure will be the Diabetes Management Self-Efficacy Scale (DMSES-UK) [23] which measures the individual’s efficacy expectations for engaging in 20 diabetes self-management activities, for example, taking daily exercise and keeping to a healthy eating plan when away from home. A sample size of 100 patients will detect a 3.5 point difference in the mean PAID score from baseline and a 9 point difference in the mean DMSES score from baseline. These calculations are based on 90% power (α = 0.05).

Additional self-report measures may be introduced to new cohorts of patients in order to test developing hypotheses generated by interviews with patients and staff. For example, if a theme emerges from the interviews suggesting that using *HeLP-Diabetes* may increase patients’ levels of physical activity, we may administer a physical activity self-report measure to a new cohort of patients at baseline, 3 months and 12 months to quantitatively explore this. Power and sample size will be calculated for each new measure prior to it being administered.

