### Data collection

After consenting to take part in the evaluation research study, patient participants will be allocated a unique study ID number and complete baseline measures. Participants will be asked to provide their email address, postal address and contact number for data collection purposes. They will be sent a link in an email to a web-based case report form which will host the data collection measures. The data entered into this form will be anonymous and only linked to the patient by the unique ID number. Participants will be asked to complete socio-demographic information at baseline and self-report measures at baseline, 3 months and 12 months. Socio-demographic information will be collected to describe the sample, and to compare intervention use and self-report measure data.

Both patient and health professional participants will be asked to take part in semi-structured interviews. Each participant may be interviewed several times throughout the course of the study. We will sample until saturation is reached. In order to capture a breadth of experiences interviews will be conducted with patients from a range of ethnic backgrounds, ages, socio-demographic statuses, length of time with diabetes, treatment types, and associated complications, as well as a range of experience with computers and the internet. Similarly, to capture a range of staff experiences, we will seek to interview consultants, salaried doctors, junior hospital doctors, general practice partners, general practice managers, practice nurses, community nurses, hospital diabetes nurses and reception staff from GP surgeries and diabetes clinics. It is likely that there will be different levels of engagement with *HeLP-Diabetes* and with the evaluation research study between different members of staff and between different services and sites. Therefore, not all interviews will be face to face; initial interviews and follow-up encounters with some participants may be short, highly focused telephone interviews. These will minimise the demand on participants, and is likely to be much more cost effective. However, more in-depth, semi structured interviews will be conducted with participants wherever possible. Participants may be sampled purposefully at times to ensure that we have captured a range of experiences and opinions.

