### Anaylsis

The proportion of GP surgeries and clinics offered *HeLP-Diabetes* who adopt it, the number of patients who register on *HeLP-Diabetes*, the socio-demographic characteristics of the patients who take part in the evaluation study and the characteristics of the clinics and GP surgeries that adopt *HeLP-Diabetes* will be described using descriptive statistics. SPSS statistical software [24] will be used for coding and analysing these data. Descriptive statistics will also be used to explain how patients make use of *HeLP-Diabetes* including counts of pages accessed, number of logins, the times of use, the duration of use and the patterns of use by different users. This data will be recorded automatically by the website software. The time and other resources expended on implementing *HeLP-Diabetes* will be recorded on a proforma and these will be collated on a spread sheet and data described descriptively.

The cost of health professional input from the GP surgeries and clinics will be based on national average rates using Personal Social Services Research Unit estimates. Estimates of the additional time required from the general practice and clinic staff where *HeLP-Diabetes* is implemented will be calculated from responses in the qualitative interviews. Resources required in training individual patients to use *HeLP-Diabetes* will be estimated.

Participant scores on the PAID and DSMSE-UK scales will be compared statistically at the different time points using a repeated measures analysis of variance test using time as the independent variable. If a statistically significant effect is found post-hoc tests will be used to explore this further. Follow up PAID and DSMSE-UK scores will be adjusted for initial scores and other baseline covariates including age, gender, and duration of diabetes. Group effects including gender and age will be assessed using mixed-between within subjects analysis of variance.

With respondents’ consent, all semi-structured interviews will be audio-recorded, transcribed (and edited to ensure anonymity of respondent) and data will be subjected to formal analysis. Patient and staff interviews will be analysed inductively to identify themes and categories, a process of constant comparison will be used to establish analytical categories. Atlas. ti [25] data collation and management software will be used to aid data management and analysis.

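### The 90% power is stated for a single difference from baseline, but the plan tests that difference only after a significant three-time-point ANOVA, so the stated power does not belong to the planned procedure

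*Protocol article*

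**What the plan says.** The sample-size statement is in the Outcomes section, under the objective on self-reported outcomes: "A sample size of 100 patients will detect a 3.5 point difference in the mean PAID score from baseline". For DMSES the corresponding figure is 9 points. Power is given as 90% with α = 0.05. The statement names no test, no follow-up time and no standard deviation, and does not say whether the 100 are recruited or analysed.

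The Data collection section sets "self-report measures at baseline, 3 months and 12 months", so two different changes from baseline exist.

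The analysis section compares PAID and DMSES scores "using a repeated measures analysis of variance test using time as the independent variable". It continues: "If a statistically significant effect is found post-hoc tests will be used to explore this further". The next sentence adds, with no condition attached: "Follow up PAID and DSMSE-UK scores will be adjusted for initial scores and other baseline covariates", the covariates including age, gender and duration of diabetes.

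The objective is exploratory. In the Objectives section it begins "To explore any effects of" HeLP-Diabetes use.

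**The concern.** The article fixes both the power claim and the analysis, and the two concern different things. The claim is about one difference between a follow-up and baseline. The planned test asks whether the three time-point means differ at all (2 numerator degrees of freedom), and only a positive answer leads to a test of a difference from baseline. A test that needs a second test to be significant first cannot have more power than the same test without that condition.

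What is at stake is how a null result is read. A report could say that the study had 90% power for 3.5 PAID or 9 DMSES points when the procedure used had a different, pattern-dependent power, and usually a lower one for the difference itself.

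**Working it through.** **Inputs from the article:** n = 100; differences 3.5 (PAID) and 9 (DMSES); power 90%; α = 0.05; three time points; omnibus test, then post-hoc tests.

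**Assumptions, not in the article:** two-sided testing; a paired test behind the stated power; sphericity; Bonferroni as one possible post-hoc correction; losses of 20% and 30% as illustrations.

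**Step 1. The plan's own figure.** It cannot be reproduced forwards because no SD is given. Solving backwards for a two-sided paired test:
- Normal approximation: SD of change = δ√n/(z₀.₉₇₅ + z₀.₉₀) = 3.5 × 10/(1.960 + 1.282) = 10.8 for PAID, and 9 × 10/3.242 = 27.8 for DMSES.
- Noncentral t: a standardised change of 0.3273 gives 90% at n = 100, so SD = 3.5/0.3273 = 10.7 and 9/0.3273 = 27.5.

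Other readings also give 90%, with another SD for PAID (normal approximation): one-sided paired 12.0; paired with α/2 9.9; paired with α/3 9.5; two independent samples of 100, 7.6. The paired two-sided reading is therefore an inference. Both scales have the same standardised change under it, so the powers below apply to both.

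**Step 2. Omnibus test, 100 complete cases.** Under sphericity the error variance is σ² = SD²/2 = 10.69²/2 = 57.2. The noncentrality is λ = n Σ(μⱼ − μ̄)²/σ², referred to F with 2 and 2(n − 1) degrees of freedom.
- Full change at both follow-ups (0, d, d) or at 3 months only (0, d, 0): Σ = 2d²/3 = 8.167, λ = 816.7/57.2 = 14.3, power 92.9%.
- Gradual (0, d/2, d) or half-fading (0, d, d/2): Σ = d²/2 = 6.125, λ = 612.5/57.2 = 10.7, power 83.7%.

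The fading pattern is not contrived: the article's Background reports that effects of such programmes on HbA1c may decline over time.

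**Step 3. Omnibus plus post-hoc confirmation of the full change from baseline.** Simulation, 100,000 replicates per pattern. The ranges cover the four patterns of step 2.

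| Complete cases | Single paired test | Omnibus alone | Omnibus, then unadjusted post-hoc | Omnibus, then Bonferroni over 3 |
|---|---|---|---|---|
| 100 | 90% | 84–93% | 83–88% | 79–80% |
| 80 | 82% | 74–86% | 73–79% | 67–68% |
| 70 | 77% | 68–81% | 66–72% | 60–61% |

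The rows for 80 and 70 matter only if 100 is the number recruited.

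**Step 4. Detectable difference at 90% power, single paired test.** With 80 pairs: 3.92 PAID and 10.09 DMSES. With 70 pairs: 4.20 and 10.80. To end with 100 pairs, recruit 100/0.8 = 125 at 20% loss, or 100/0.7 = 143 (rounded up) at 30%.

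**The case against.** The other side has several sound points, and they limit the finding.

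- **The test behind the 90% is not stated.** A reader might infer that it can only be a single paired test in 100 complete pairs. Step 1 shows that other tests fit with other SDs. If a Bonferroni-corrected calculation was used, much of the post-hoc shortfall with 100 completers goes away.
- **100 recruited is not in the text.** A reader might infer that 100 patients are enrolled and then eroded by dropout. The words fit 100 analysed equally well, nothing caps recruitment at 100, and no loss rate is given. Under the analysed reading the attrition rows do not apply.
- **The omnibus need not lose power.** For a change that is sustained, or present only at 3 months, it has 93%, above the stated figure. A general claim that the stated differences are not delivered is not supported.
- **The condition falls on post-hoc tests, not on estimation.** A reader might infer that a real change could go unestimated. The baseline-adjusted comparison carries no such condition, and nothing prevents mean changes being reported. Adjustment could also raise or lower power by an amount that cannot be worked out here.
- **This is a condensed article.** The SDs, any allowance for loss and the post-hoc method may sit in the full protocol. Their absence is not the point made here.
- **The objective is exploratory** and the last of four.

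What remains is the mismatch between two statements that the article does make. No fuller document can make the power of an unconditional difference from baseline the power of a conditional one, unless it changes the analysis or restates the power.

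**Conclusion.** The point holds as a mismatch between the power statement and the analysis, not as a proven arithmetic error. The stated 90% concerns one difference from baseline at an unnamed follow-up, while the plan reaches a test of that difference only through a significant three-time-point ANOVA.

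On the two-sided paired reading, with sphericity and 100 complete cases, the loss for the confirmed difference is about 2 to 7 percentage points with unadjusted post-hoc tests (83 to 88% against 90%). It is about 10 to 11 points with Bonferroni. Anything larger depends on 100 being the number recruited and on an assumed loss. Given the exploratory objective, this is a matter of matching the analysis to its own justification. It is no reason to doubt that the study is worth doing.

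**What to change.** 1. In the analysis section, pre-specify the mean change from baseline at one named follow-up as the contrast that the sample size refers to, for each scale.
2. Test and report both the 3-month and the 12-month changes with 95% confidence intervals, whatever the ANOVA shows. The ANOVA can stay as a summary of the time course.
3. Restate the power sentence as applying to that contrast in 100 patients with data at that time point. If 100 is the number recruited, quote the larger detectable differences instead, for example 3.9 PAID and 10.1 DMSES with 80 completers, or 4.2 and 10.8 with 70. These figures assume the back-solved SDs and should be replaced if the actual planning SDs differ.

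Cost: one changed analysis sentence and a restated power sentence, with detectable differences that may look slightly less favourable. No extra patients or visits are needed. Dropping the condition gives up whatever error control the omnibus offered; naming a single contrast per scale keeps that contrast at its own 5% level.
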